### Primary Outcome: Complete Prevention of Mother-to-Child Transmission of HIV Retention

The primary outcome is complete PMTCT retention, measured from the first PMTCT appointment until the infant’s first HIV test, which is targeted at 6 weeks of age. The aggregate measure of complete retention—calculated as retention before delivery, at delivery, and after delivery—will be dichotomously coded as complete or incomplete retention. Complete retention is defined as maternal ART initiated (if not already on ART at the time of pregnancy), all scheduled PMTCT appointments attended, hospital-based delivery, and HIV DNA PCR testing by 6 weeks (<7 weeks) postnatal.

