#### Prevention of Mother-to-Child Transmission of HIV Appointment Attendance

We will measure the proportion of mothers who attended all scheduled ANC appointments, documenting late (>7 days past scheduled date) and missing (>14 days past scheduled date) attendance. The number of possible appointments will vary on gestational age at PMTCT enrollment; thus we will measure the median number of visits, the proportion who received the recommended 4 or more appointments, and the proportion enrolled by the recommended 14 weeks gestation.

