#### Statistical Analyses

To examine the baseline participant and facility characteristics, we will calculate descriptive statistics including proportions for categorical variables and means (SD) or median (interquartile range) for continuous variables [47]. For the primary outcome, chi-square tests will be used to compare the proportion with complete PMTCT retention between groups [48]. We will explore correlations between complete PMTCT retention and possible predictors (eg, knowledge, motivation to complete care, maternal HIV disclosure, perceived benefit of ART, maternal depression, and risk of intimate partner violence) using Phi, point-biserial, or Spearman rho statistics depending on the measurement level of each predictor [49]. Analytic models will control for significantly different preintervention covariates across conditions and hospitals, clustered observations (eg, time nested within setting), and gestational age as it impacts the eligible/recommended number of appointments or services.

For secondary analyses, Kaplan-Meier curves will illustrate differences in the duration of PMTCT retention before, during, and after delivery, accounting for the woman’s eligible period of engagement (based on the timing of enrollment and accounting for premature infant or maternal mortality). We will then identify time periods when meaningful decreases in PMTCT retention occur, using Cox proportional-hazard regression for survival analyses (ie, retention), if all assumptions are met [50]. Known variables associated with HIV service retention (age, disclosure status, educational level, and number of children [22,51,52]) and those correlated (*P*<.10) will then be included in a generalized linear mixed model to identify a parsimonious list of predictors.

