Using chi-square tests, we will compare the proportion of pregnant women (1) attending all scheduled PMTCT appointments (4 or more PMTCT visits and late or missed visits), (2) tested for VL (VL sample collected, results returned, and detectible VL values), (3) delivery at the hospital, (4) enrolling in EID (dried blood spot sample collected by <7 weeks), and (5) have an infant diagnosed with HIV, between intervention and control sites. The median number of PMTCT appointments, median gestational week at first PMTCT appointment, and median TAT for VL results will be calculated and compared using Mann Whitney *U* tests. Although medication adherence documentation at the control site (typically described as poor, fair, or good) will not permit direct comparison, the proportion of pregnant women at the intervention site with >95% adherence will be described. Participant preferences for the content and frequency of SMS text messages for medication adherence support will also be described. *P* values will be adjusted (using Tukey correction) for multiple tests, where appropriate. Quantitative data will be analyzed using Statistical Application Software (SAS) version 9.4.

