## Discussion

Previous HITSystem pilot data and studies have demonstrated significant success in improvement of EID outcomes particularly in improving the efficiency and quality of key EID outcomes [32-34,38]. Leveraging the improved linkage of health facilities, mother-infant pairs, and laboratories in the context of EID, the HITSystem 2.0 (PMTCT) will expand the current Web-based platform to bridge the gap between maternal and pediatric HIV services. Outcomes at each step of the PMTCT cascade will be analyzed, and specific challenges will be identified.

This study will design and implement the HITSystem 2.0 through formative qualitative research, intervention development using the 4Ds process, and a pilot implementation period as described above. It will also provide user satisfaction data by highlighting the HITSystem 2.0’s usefulness, acceptability, challenges, and recommendations to improve the intervention. The proposed HITSystem 2.0 will integrate maternal and infant HIV services in one system-level, Web-based intervention that will provide linked, prospective data for mother-infant pairs, which has been identified as a problematic gap in the current system. The findings of this study will refine the HITSystem 2.0 intervention, particularly tracking and utilization of challenging measures such as medication adherence and antenatal VL results to enhance system performance and implementation strategies in a larger scale efficacy trial.

Although this intervention will focus on health system improvement to enhance quality of care for women and infants in the facility setting, the study will not directly target PMTCT uptake, which would require community-based outreach. Given that intervention site data will be tracked via the HITSystem whereas control site data will be captured via disparate paper-based registries and patient files, there may be discrepancies in data quality and documentation of services rendered between control and intervention sites; all efforts will be made to capture any available data at control sites to minimize this limitation. As the study design and implementation evolve, we anticipate that eHealth technologies in the study regions will likewise evolve and influence the standard of PMTCT care. These external factors will be documented and accounted for in the design and analyses.

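### The primary test is an unadjusted chi-square although gestational age at enrolment sets how many visits must be attended; other covariates are chosen by baseline significance, and gestational age at entry is tested among the outcomes

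*Protocol article*

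**What the plan says.** All references are to the Protocol article.

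- **Primary Outcome.** Complete retention is all-or-none. Besides ART initiation it requires "all scheduled PMTCT appointments attended, hospital-based delivery, and HIV DNA PCR testing by 6 weeks (<7 weeks) postnatal".
- **Appointment Attendance (Secondary Outcomes).** "The number of possible appointments will vary on gestational age at PMTCT enrollment". The same paragraph lists the proportion of women enrolled by 14 weeks as a measure.
- **Statistical Analyses, primary test.** "For the primary outcome, chi-square tests will be used to compare the proportion with complete PMTCT retention between groups". Power and Sample Size is built on that test alone.
- **Statistical Analyses, adjustment.** Later in the same paragraph: "Analytic models will control for significantly different preintervention covariates across conditions and hospitals". The sentence goes on to clustered observations and to "gestational age as it impacts the eligible/recommended number of appointments or services". The only models named, a Cox regression and a generalized linear mixed model, are in the next paragraph, on secondary analyses. Age and number of children enter the mixed model, whose purpose is to find predictors.
- **Statistical Analyses, secondary comparisons.** "median gestational week at first PMTCT appointment" is compared between sites by Mann-Whitney test, alongside the outcome comparisons.
- **Discussion.** "the study will not directly target PMTCT uptake". The intervention specifications place entry into the system at the first PMTCT appointment.

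**The concern.** A woman who enrols late has fewer scheduled visits, so fewer chances to fail an all-or-none outcome. The protocol recognises this, since it is the reason given for controlling for gestational age. But a two-group chi-square takes no covariates, and no adjusted model is tied to the primary comparison. Once results are known, either the unadjusted or an adjusted figure could be presented as the main one.

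The rule for the other covariates depends on sample size and on chance. It takes no account of how strongly a covariate predicts retention, and it lets the data choose the model.

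Gestational age at the first visit is settled before a woman meets the intervention. A site difference in it, or in enrolment by 14 weeks, reflects who enrolled. Placed among the outcomes it can be misread as a result.

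The hospitals are described as matched on resources, caseload and broad patient profile. With one hospital per arm, though, women are not individually randomized, and only the intervention site requires phone access. Individual case-mix balance is therefore not assured.

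**Working it through.** **1. The plan's own figure.** Inputs from Power and Sample Size: 47% vs 20%, two-sided alpha 0.05, power 80%, 54 per arm.

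- Without continuity correction: n = [1.96·√(2·0.335·0.665) + 0.842·√(0.47·0.53 + 0.20·0.80)]² / 0.27² = 46.8, so 47 per arm.
- With continuity correction: (46.8/4)·[1 + √(1 + 4/(46.8·0.27))]² = 53.9, so 54 per arm and 108 in total, as stated.
- Reading 0.27 as Cohen's w with 1 df gives a total of 107.7, which also rounds up to 108.

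The figure reproduces, and it covers the unadjusted chi-square only.

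**2. How often the significance rule detects an imbalance.** Power of a two-sided 5% baseline comparison with 54 per site is Φ(d·√(54/2) − 1.96), where d is the imbalance in SD units.

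| d | d·√27 − 1.96 | Detected |
|---|---|---|
| 0.2 | −0.92 | 18% |
| 0.3 | −0.40 | 34% |
| 0.4 | 0.12 | 55% |
| 0.5 | 0.64 | 74% |

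**3. How visit number moves the outcome with identical care.** Assumptions, not document figures: visits are attended independently with probability q, and complete retention is 20% at four visits (20% is the protocol's control rate). Retention with k visits is then 0.20·q^(k−4).

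| q | 3 visits | 4 visits | 6 visits |
|---|---|---|---|
| 0.80 | 25.0% | 20% | 12.8% |
| 0.90 | 22.2% | 20% | 16.2% |

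**4. False-positive rate with no intervention effect.** Assumptions: 54 per site, overall mean gestational age at enrolment 22 weeks (SD 7), a visit every four weeks until week 40, overall retention about 20%, uncorrected chi-square, 2,000 simulated trials per setting. Near 5%, the simulation standard error is √(0.05·0.95/2000) ≈ 0.5 points.

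| Site difference (weeks) | 0 | 2 | 3 | 4 | 6 |
|---|---|---|---|---|---|
| Chi-square, q = 0.80 | 5.0% | 4.9% | 7.5% | 7.5% | 13.8% |
| Chi-square, q = 0.90 | 4.4% | 4.9% | 4.7% | 5.6% | 7.6% |

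A logistic model that always included gestational age stayed between 4.0% and 5.3% in all ten settings.

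**5. Can the data carry an adjusted model?** Expected events at the planned rates: 54·0.20 + 54·0.47 = 10.8 + 25.4 ≈ 36. A model with site and four single-term covariates has five coefficients besides the intercept: 36/5 ≈ 7 events each. That is workable for a short list, with little room for more.

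**The case against.** **The protocol does plan to adjust for gestational age.** This stands. Gestational age is named unconditionally and is exempt from the significance rule. A reader might infer that it is ignored, or adjusted for only if the sites differ significantly; the text supports neither. The sentence also sits in the primary-outcome paragraph, so it can be read as a chi-square followed by adjusted models of complete retention. Even so, the protocol would then have two analyses of the primary outcome, with only the unadjusted one named and powered.

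**Model form may be left to a fuller document.** Fair for detail such as the link function. But the chi-square as primary test and the significance criterion are stated choices, not omissions.

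**Prognostic variables are not ignored throughout.** Correct: age and number of children are in the mixed model without a baseline-difference condition. That model is secondary and seeks predictors.

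**The hospitals are matched, and historical data are collected.** Both stand. To call the sites unmatched would contradict Trial Design. The 18 months of retrospective data offer another handle on site differences. Neither assures balance in gestational age among the enrolled women.

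**The bias is small.** Largely stands. At q = 0.90 the false-positive rate remains close to 5% up to a 4-week difference. In the same simulation, adjusting only when gestational age differed significantly gave 3.9 to 5.3%, so it shows no error inflation from a significance screen. The detection rates in step 2 are not a measure of bias either, because no covariate-outcome association is given. It is also tempting to treat the protocol's 68% antenatal retention as attendance at four visits and derive a cost per visit. The Background shows that 68% is the complement of the 31.9% of women with a gap in care of more than 30 days, so it cannot carry that reading.

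**Testing gestational age is only a matter of placement.** Partly. Nothing says that a difference would be credited to the intervention, and the Discussion disclaims targeting uptake. The placement still conflicts with its use as a covariate.

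**Conclusion.** The point holds in three limited parts. The named primary test cannot carry the adjustment that the protocol itself considers necessary. The remaining covariates for the adjusted models are chosen by a poor rule. A pre-exposure variable is listed and tested among the outcomes.

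The likely bias is small when the sites differ modestly in gestational age and grows with the difference. The figures in steps 3 and 4 are illustrations that rest on independent visits, an assumed per-visit attendance and an assumed distribution of gestational age. The documents give no site-level gestational age, so the actual size is unknown. A reader might infer that the primary result will be seriously wrong, or that adjustment would rescue a comparison of two hospitals. The documents support neither: the planned difference is 27 points, and with one hospital per arm no covariate model separates the intervention effect from the hospital effect. The change should be made because it removes a known, measured source of difference and settles in advance which adjusted estimate counts.

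**What to change.** - Take the adjusted primary estimate from one prespecified model of complete retention, for example a logistic model reported as a standardised risk difference with a confidence interval.
- Fix its covariates now: gestational age at enrolment, ART status at enrolment (new or already on treatment), age and number of children. Age and number of children are routine data at both hospitals; the outcome definition and the planned comparisons already need ART status and gestational age.
- Delete the rule that admits covariates by significant baseline difference.
- Keep the chi-square as the unadjusted companion.
- Report gestational week at first visit and enrolment by 14 weeks as baseline characteristics, without an outcome test.

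The cost is analysis-plan wording, slightly more analysis work and a few more parameters on about 36 expected events, which is a reason to keep the list short. The Results section says that no between-arm analysis had been done when the article was written, so at that stage the change could be made without knowledge of the outcomes.

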### Secondary Outcomes

#### Duration of Prevention of Mother-to-Child Transmission of HIV Retention

We will estimate the duration (number of weeks) of PMTCT retention for each participant by subtracting the last date of documented service engagement from the date of enrollment. This will allow comparisons between total time retained in PMTCT services between groups and identify when (antenatal, delivery, or early postnatal) disengagement from PMTCT most often occurs.

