#### Power and Sample Size

The required sample size was calculated to compare differences in proportions of complete PMTCT retention for the intervention (p1) and control (p2). We estimated complete retention by combining available retention data from Kenya for each phase: antenatal retention (68%) [19], hospital-based deliveries (61%) [36], and postnatal retention for HIV-exposed infants within 12 weeks (54.9% [21] to 80.7% [20]; average 67%). Recognizing that these estimates do not represent cumulative risk for the same individuals, we conservatively estimate complete PMTCT at the control site to be 20%. Our EID pilot data showed that retention doubled at 9 months with retention rates as high as 94.2% [33]. Using a midrange between differences achieved from published studies and our own pilot study, we conservatively estimate complete retention of 47% for HITSystem 2.0 participants. A sample size of 108 (54 intervention and 54 control participants) is needed to achieve 80% power to detect a significant difference in the proportion of complete PMTCT retention with chi-square tests (goodness of fit test: contingency table) with an effect size of 0.27 and a 2-tailed alpha of .05. Accounting for the proportion with mobile phone utilization, and 1.5% maternal mortality [45] and 3.7% [46] perinatal mortality, we estimate n=70 eligible participants. During Phase 3 enrollment, we plan to enroll n=54 of the n=70 eligible PMTCT patients per hospital. On the basis of our initial HITSystem pilot where <1% of women declined, we anticipate high participation.

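### The timing of disengagement is assigned to a Cox model that, as named, gives time-constant hazard ratios and does not show when retention falls

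*Protocol article*

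**What the plan says.** Under Secondary Outcomes, the duration of retention has two purposes. One is to compare total time retained between groups. The other is to "identify when (antenatal, delivery, or early postnatal) disengagement from PMTCT most often occurs".

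The Statistical Analyses section then gives two steps. First, "Kaplan-Meier curves will illustrate differences in the duration of PMTCT retention before, during, and after delivery". Second, "We will then identify time periods when meaningful decreases in PMTCT retention occur, using Cox proportional-hazard regression", with the condition "if all assumptions are met". The article does not list the terms of that Cox model. It mentions no period covariate, time-by-site term, baseline-hazard estimate or dropout rate by period.

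Two other parts of the article matter here. Duration is counted from enrollment, and the section on appointment attendance notes that gestational age at enrollment varies. Table 1 ties intervention components to particular times: appointment reminders, delivery reminders 4 and 2 weeks before the due date, and provider alerts that run up to the infant-testing link.

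**The concern.** The question is in which period retention drops. A Cox model with fixed covariates answers a different one: whether the hazard of disengaging is proportionally higher or lower for one group or covariate value than another, averaged over follow-up. A significant result does not mean that any period is worse than the others. A null result does not mean that none is.

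The condition on assumptions adds to the difficulty. If the delivery reminders work mainly around delivery, the hazard ratio changes over time and proportional hazards fails. Read literally, the plan then drops the named timing analysis. If the check misses the violation, one averaged ratio hides the period.

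At stake is what the pilot says about where women are lost. The Discussion intends the findings to refine HITSystem 2.0 for a larger efficacy trial. A Cox p-value could be taken as evidence about timing that it does not contain.

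**Working it through.** **1. The plan's own figure.** The only computed figure is for the primary chi-square comparison: "A sample size of 108 (54 intervention and 54 control participants) is needed to achieve 80% power". Inputs from Power and Sample Size: 47% and 20%, two-sided alpha 0.05.

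- Mean proportion = (0.47 + 0.20)/2 = 0.335.
- n per arm = [1.960 × √(2 × 0.335 × 0.665) + 0.842 × √(0.47 × 0.53 + 0.20 × 0.80)]² / 0.27² = 46.8, so 47.
- With continuity correction: (46.8/4) × [1 + √(1 + 4/(46.8 × 0.27))]² = 53.9, so 54.

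The figure reproduces. The present point does not depend on it, and no figure is given for the Cox analysis.

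**2. What the Cox fit uses.** The partial likelihood is the product, over observed events i, of exp(βx_i) / Σ exp(βx_j), summed over the women j still at risk. The baseline hazard cancels. With fixed covariates, only the order of event times enters.

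**3. Illustration.** One trial of 54 + 54 women was simulated. The generating hazard ratio was ln 0.47 / ln 0.20 = 0.469, which treats complete retention as survival to the end of follow-up. Follow-up of 36 weeks, split at weeks 26 and 30, is assumed. The event order was held fixed while dropout times were moved.

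| Dropouts antenatal/delivery/postnatal | Cox HR | SE (log HR) | p | Breslow cumulative hazard, weeks 26/30/36 |
|---|---|---|---|---|
| 63/8/5 | 0.591 | 0.232 | 0.0235 | 1.10/1.36/1.55 |
| 13/58/5 | 0.591 | 0.232 | 0.0235 | 0.15/1.36/1.55 |
| 13/8/55 | 0.591 | 0.232 | 0.0235 | 0.15/0.26/1.55 |

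The regression result is the same in each row. Only a separate baseline estimate, which the plan does not name, tells the rows apart. The illustration puts every woman in the same period at the same week and uses no period covariate.

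**4. Simulated tests.** Assumed: 54 per arm, entry at 12 to 32 weeks gestation, three delivery-anchored periods, test level 0.05. The site-only Cox and Poisson columns use 600 trials per scenario. The last column is a separate run of 300 trials, in which up to 9 fits per scenario failed and hazards given only as ratios had to be filled in.

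| Scenario | Cox, site term only | Poisson period test | Cox, time-varying period term |
|---|---|---|---|
| Flat hazard, sites equal | 3% | 6% | 3% |
| Flat hazard, sites differ (0.040 vs 0.015 per week) | 90% | 4% | 5% |
| Six-fold peripartum peak, sites equal | 6% | 99.8% | about 100% |
| About seven-fold postnatal peak, sites equal | 6% | 100% | 100% |

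The contrast is between a model without period terms and one with them. It is not between Cox and Poisson.

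**5. Period-specific site effects.** For a postnatal-only effect (0.10 vs 0.02 per week), rejection was 33% for the Cox site test, 61% for Poisson site-by-period and 62% for Cox site-by-period. A residual check of proportionality flagged it in 28% of trials. For a peripartum-only effect the figures were 65%, 67% and 52%, with 15% flagged. The hazards for that scenario were not matched between the two runs, so 67% and 52% should not be compared closely.

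**6. Precision.** If every woman without complete retention disengaged, events would number about 0.80 × 54 = 43 and 0.53 × 54 = 29. That is 72 over six site-by-period cells, or 12 on average. Women who missed one visit but stayed in care make the true number smaller. With d events, the 95% interval for a hazard runs from the estimate divided by to multiplied by exp(1.96/√d): a factor of 4.0 at d = 2, 1.8 at d = 12 and 1.5 at d = 20.

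**The case against.** The strongest reply is that Cox regression can be made to answer the question. Because duration runs from enrollment and gestational age at enrollment varies, women are in different periods at the same week of follow-up. A time-varying period term is then estimable, and the last column of the table shows that it works. The article is condensed, and the coding of covariates is commonly left to a fuller document. This stands, and it rules out saying that Cox regression cannot address timing. What remains is that the article ties the named method to this purpose and names none of the terms that would make it fit.

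Second, timing is covered elsewhere. The Kaplan-Meier curves carry no condition, last-engagement dates can be tabulated by period, and chi-square tests compare the sites on appointments, hospital delivery and infant testing. This also stands as a descriptive view. A reader might infer that the study cannot find where women are lost, and the document does not support that.

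Third, the clause on assumptions is an ordinary safeguard and applies only to the Cox step. That is fair. A reader might infer that the analysis would be dropped exactly when there is something to find, but a check that flags 15% to 28% of trials would seldom trigger this.

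Fourth, a Cox site test that rejects when the sites differ is behaving correctly, and the duration outcome does include a between-group comparison that Cox serves. This stands too. The 90% shows only that such a rejection says nothing about periods.

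**Conclusion.** The point holds as a mismatch of method and purpose in one secondary analysis. As named, with fixed covariates, the Cox model yields time-constant hazard ratios and does not show when disengagement occurs. This follows from the form of the partial likelihood and needs no assumed hazards. Making the step conditional on proportional hazards suits the aim poorly, because a period-specific effect would itself break that assumption.

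The simulated percentages rest on assumed hazards that are not tied to the plan's 20% and 47%, and they serve only as illustration. A general loss of power is not shown: the Cox site test falls well behind the interaction test for the postnatal-only effect (33% vs 61%) but not for the peripartum-only effect (65% vs 67%). The primary chi-square comparison and the sample size of 108 are unaffected. The change is worth making before outcome data are compared. The Results section says that no such comparison has been done.

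**What to change.** Assign the timing question to dropout hazards in three periods (antenatal, peripartum, early postnatal), anchored on each woman's delivery date, or on her due date where delivery is unknown. A piecewise-exponential, discrete-time or life-table analysis would do. A Cox model with a time-varying period term and a site-by-period interaction also serves for relative hazards. Define the period boundaries in advance. Report the estimate and confidence interval for each period and site, with tests of period and of site-by-period. Do not make this analysis conditional on proportional hazards. Keep the simple Cox model as an overall between-group or covariate summary, with its assumption check.

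The cost is a sentence or two in Statistical Analyses, with the same data and software. The drawback is precision: the simulations gave roughly 2 to 20 events per site and period, so intervals will be wide and the results should be labelled exploratory.

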### Phase 3: Trial Intervention

#### Trial Design

We will employ a matched, randomized pilot study design in 2 government hospitals with comparable resources, patient volume, and basic patient characteristics. One hospital will be randomized to receive the HITSystem 2.0 intervention and the other hospital will maintain standard of care PMTCT services. An extended 18-month implementation period will allow 9 months to reach the sample size requirement of n=54 at each hospital and another 9 months to ensure complete prospective outcome data from the first PMTCT appointment in pregnancy until the infant’s first HIV DNA PCR test result is determined. This follow-up period will assess complete retention throughout PMTCT services, ART adherence, and rates of infant HIV transmission. We will also collect retrospective PMTCT outcome data from each hospital for the 18 months before implementation to facilitate pre- and postcomparisons at the same facility.

Satisfaction interviews with HITSystem 2.0 users (HIV positive women and providers) will inform barriers to use that can be targeted either through future strategic refinement of the design or collaboration with key partners to address constraints beyond the scope of this intervention.

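### With about 36 complete-retention events, the P<.10 screen feeding a mixed model is prone to overfit, and a hospital random effect cannot be estimated if complete retention is the response

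*Protocol article*

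**What the plan says.** Statistical Analyses describes two steps. First, complete retention is correlated with possible predictors. Six are named as examples: knowledge, motivation, disclosure, perceived benefit of ART, depression and partner-violence risk. Second, four variables enter without screening: "Known variables associated with HIV service retention (age, disclosure status, educational level, and number of children". These four and whatever passed P<.10 "will then be included in a generalized linear mixed model to identify a parsimonious list of predictors". The same section asks analytic models to control for gestational age, for covariates that differ between conditions and hospitals, and for clustering. It sets no limit on the number of terms. It does not name the response or the random effect of the mixed model.

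The outcome used in the correlation step "will be dichotomously coded as complete or incomplete retention", so each woman contributes one value. On design, Trial Design says "One hospital will be randomized to receive the HITSystem 2.0 intervention and the other hospital will maintain standard of care PMTCT services". The expected event count follows from Power and Sample Size: "we conservatively estimate complete PMTCT at the control site to be 20" (per cent), and "we conservatively estimate complete retention of 47% for HITSystem 2.0 participants".

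**The concern.** Choosing variables by univariable P value and then fitting them to the same small data set makes chance associations look like predictors and enlarges the coefficients of real ones. Few events make both problems worse. The mixed model raises a second issue: with one hospital per condition, a random effect for hospital has nothing to be estimated from once condition is in the model.

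What is at stake is how the predictor list is read. The Discussion says the study's findings will refine the system ahead of a larger efficacy trial. A list with unsupported entries, or with overstated effects, is a weak basis for deciding which women need extra support.

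**Working it through.** **Planning figure.** Inputs from Power and Sample Size: "A sample size of 108 (54 intervention and 54 control participants) is needed to achieve 80% power", "with an effect size of 0.27 and a 2-tailed alpha of .05", 47% against 20%. The pooled two-proportion formula gives (1.96·√(2·0.335·0.665) + 0.8416·√(0.47·0.53 + 0.20·0.80))² / 0.27² = 46.8, or 47 per arm. With the continuity correction this becomes 54 per arm, 108 in total, as stated.

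**Events.** 54 × 0.47 + 54 × 0.20 = 25.4 + 10.8 = 36.2 women with complete retention.

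**Terms.**
- Named candidates: 4 entered directly + 6 screened − 1 (disclosure is in both lists) = 9 distinct.
- Adding gestational age and hospital: 11 candidate terms; 36.2 / 11 = 3.3 events per candidate.
- Fitted on average in the simulation below: about 7 terms; 36.2 / 7 = 5.2 events per term.
- Even with no real predictor, the five distinct screened variables send 5 × 0.10 = 0.5 through on average, and at least one passes in 1 − 0.9⁵ = 41% of studies.

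**Simulation of the procedure.** Set-up: 108 women at 20% and 47%; the four known variables, gestational age and a fixed hospital term always in; five variables screened at P<.10 on the correlation with the outcome. Assumed, because the protocol does not give them: independent, normally distributed predictors, and a final list formed at P<.05.

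| True state | At least one noise variable listed | Noise share of list | Median calibration slope in new women |
|---|---|---|---|
| No real predictor | about 39-40% | 100% | 0.49 |
| Two real, OR 1.5 per SD | about 31% | about 30-33% | 0.55 |
| Two real, OR 2.0 per SD | about 31% | about 19% | 0.66 |

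A slope below 1 means the fitted coefficients are too large on average. In the second row, real effects that reach significance average an odds ratio of about 2.0: ln 2.0 / ln 1.5 = 0.693 / 0.405 = 1.7 times the true log odds ratio.

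**What drives the noise count.** Testing ten candidates (nine plus gestational age) at 5% gives 1 − 0.95¹⁰ = 40%, close to the first row. Testing four gives 1 − 0.95⁴ = 19%. A prespecified four-variable model gave 14-18% in simulation. The gain therefore comes mainly from testing fewer variables.

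**Hospital random effect.** Two hospitals provide two hospital-level values. The intercept uses one and condition uses the other: 2 − 1 − 1 = 0 degrees of freedom remain for a between-hospital variance. With one outcome per woman, there is no within-woman correlation to model either.

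**The case against.** Several points on the other side are sound.

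- A reader might infer that about a dozen variables are screened and all fitted. The text names six for screening, as examples; four others bypass the screen, and only those passing join them.
- A reader might infer that the list will be mostly noise. That needs nearly every candidate to be null, yet the protocol cites sources for its four known correlates. With three real predictors at OR 2.0, a simulation of the nine named candidates without gestational age put the noise share at 11%.
- The chance of a noise entry is largely ordinary multiplicity, as the working shows. With 12 variables and no real predictor it was 45% with screening and 49% with all 12 fixed in advance. Deleting the screen without cutting the number of terms would not lower it.
- A reader might infer that no random effect of any kind is usable. The response is not stated; the sentence follows the analysis of retention before, during and after delivery, and the section mentions time within setting. A phase- or visit-level response could support a woman-level intercept. Leaving that structure to a fuller plan is normal for an article.
- The analysis is secondary, and the correlation step is described as exploration. Multiplicity adjustment is promised where appropriate, though not specifically for this model. No passage says the predictor list itself will shape the next trial.

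These points narrow the concern. They leave in place a fixed P<.10 screen on about 36 events with no limit on terms, and a hospital random effect ruled out by the design.

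**Conclusion.** The point holds in limited form. The procedure as written has about 3.3 events per candidate and about 5 per fitted term. It would list at least one noise variable in roughly 31-40% of such studies. Noise would be about 19-33% of the list when two predictors are real at OR 1.5 to 2.0 per SD, and a true OR of 1.5 would be reported as about 2.0 when significant. These figures rest on the planning rates, independent predictors and a final P<.05 rule. More or stronger real predictors lower the noise share.

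The statement on the random effect is conditional: if complete retention is the response, a hospital random effect cannot be estimated. The consequence is confined to interpretation of the predictor list; the primary chi-square comparison is not touched.

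**What to change.** Delete the P<.10 screening step. For complete retention, fit ordinary logistic regression with hospital as a fixed term, understood to carry intervention and hospital together. Fix a small set of predictors in advance, for example the plan's own four known correlates, or a subset of them with gestational age. Examine the remaining survey variables only in a penalised logistic model with hospital unpenalised, or descriptively. Report optimism-corrected estimates, show every prespecified coefficient with its interval whether or not it is significant, and call the predictor list hypothesis-generating. If a mixed model is kept for a repeated response, name that response and its random effect.

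The cost is analysis-plan wording and some programming; no new data are needed. The Results section reports that no comparison of outcomes between the sites had been made, so at that stage the change could be made without knowledge of them. The downside is that fewer predictors will be declared significant.
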